#### Training of Therapists and Treatment of Participants

An intervention guideline is developed that outlines how the treatments (implicit and explicit conditions) should be delivered. The main aim of the intervention is to improve the quality of walking performance in people after stroke. The basic principle of the intervention guideline is based on the definitions of implicit and explicit motor learning by Kleynen et al [11]. For the purpose of this study, we strive to create the largest contrast between the conditions as possible. The main characteristics and differences in instructions, and feedback of the practice between interventions are described in Figure 1. Both conditions will always be applied to an extent that is feasible for the participant, and training will therefore always be tailored to the participant’s abilities within the given boundaries of the condition. Similar situations will be adopted in both conditions with regard to the “organization” of the training, for example, use variation in the (analogy) instructions and practice of the motor skill.

The chosen intervention period was based on a preliminary study of Kleynen et al [28] that demonstrated that 3 weeks was a feasible period to develop and practice analogies with people after stroke. All participants will receive 9 training sessions in a 3-week intervention period, that is, 3 training sessions per week (Figure 2). Each training session takes place at the home of the participants and lasts for 30 min. Participants were asked to use the instructions in daily life (unguided therapy) and after the 3-week intervention period. To standardize the training content as much as possible, the therapists involved in the study will be trained before the start of the study. During 5 standardization training sessions, the intervention guideline will be discussed, explicated, and the therapists will be trained with the help of example cases. During the trial, therapists will attend 3 evaluation sessions to discuss the progress of the study and possible cases or difficulties they may experience during the intervention.

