### Process Evaluation

To gain an insight into the process-related factors that may have influenced the effectiveness of the 3-week analogy learning walking intervention, a process evaluation will take place along the study [55]. Data will be collected to (1) asses to what extent the therapists delivered the interventions as intended (fidelity), (2) explore the therapists’ opinions and experiences about the interventions with regard to the feasibility and possible effects, and (3) explore the patients’ opinions and experiences about the interventions with regard to the feasibility. Table 2 represents the data collection methods used to assess the different aspects of the process evaluation. For both groups, the provided instructions will be documented and evaluated in the therapists’ logs. In addition, short questionnaires will be used to administer the therapists’ and participants’ opinions about the gait training after the completion of the 3-week intervention. To explore the extent to which the interventions were implicit or explicit in nature, the verbal protocol will be assessed. Evidence indicates that implicit learning is typically characterized by the less accumulation of explicit rules compared with explicit learning [24,56].

To monitor the integrity of the intervention, self-reported (subjective) and audio-recorded (objective) data will be evaluated. First, all therapists are required to self-report any deviations from the treatment protocol or other incidents during the session in a log after every session. All instructions used during therapy sessions will be recorded in the therapists’ and patients’ logs. Furthermore, patients can use the log to write down any possible events that might have occurred during unguided therapy. The patient log is, therefore, only used as a reminder for unguided therapy and as a communication tool between therapists and participants. Second, 10 gait trainings will be randomly selected (5 implicit and 5 explicit interventions) and audio recorded. Both self-reported and audio-recorded data will be screened to evaluate whether the intervention was delivered according to the protocol.

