### Data Analyses

Baseline scores of demographic and prognostic data and primary and secondary outcome measures will be used to compare the 2 groups. Only data of the participants who attended minimum of 7 or more of the therapy sessions will be considered as adherent and processed in the statistical analysis. Statistical analysis will be conducted to determine significant differences between groups and over time (baseline and postintervention performance). A repeated measure analyses will be used to compare the 2 groups (implicit and explicit) at 3 different time points (before, after, and after 1-month follow-up). Post hoc tests with correction for multiple testing will be used to explore effects over time and between groups. Subgroup analysis will be performed on cognition (MoCA score <21) [35]. An alpha level of .05 will be set for all tests. The primary outcome measure, walking speed, will also be described with reference to clinically relevant differences between groups (MCID: 0.16 m/s) [33]. All datasets used or analyzed during this study are available from the corresponding author on a reasonable request.

Data will be analyzed according to an intention-to-treat and per-protocol principle. In the intention-to-treat, data of the participants are analyzed according to their original treatment allocation. If self-reported (subjective) and audio-recorded (objective) data reveal that cases are not delivered as intended, then the analyses will be performed using the per-protocol principle. Within this study, protocol deviations are defined as “deviations from the protocol that occur in two or more sessions.” If protocol deviations were observed, then data from this person were not included in the per-protocol analysis. Data in the process evaluation related to the therapists’ and patients’ opinions and experiences toward the feasibility of the intervention and perceived benefits will be analyzed by means of descriptive statistics. Free comments and clarifying examples may be quoted and used to describe personal experiences of the therapists or participants.

**Table 2 table2:** Measures for the process evaluation. A checkmark indicates with which measure the question is examined.

Questions	Measures			
	Therapist Log	Audio recordings	Therapist questionnaire	Patient questionnaire
To what extent did the therapists deliver the interventions as intended (fidelity)?	✓	✓	✓	

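### The population behind the primary result is not fixed: neither intention-to-treat nor per-protocol is named primary, per-protocol depends on fidelity data, and an attendance filter covers the whole analysis

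*Protocol article*

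**What the plan says.** Four statements in the protocol article, Methods, Data Analyses, bear on who is analysed.

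- Attendance: "Only data of the participants who attended minimum of 7 or more of the therapy sessions will be considered as adherent and processed in the" (the sentence ends by referring to the statistical analysis as a whole). This comes before any analysis set is mentioned.
- Analysis sets: "Data will be analyzed according to an intention-to-treat and per-protocol principle". ITT is described only by how people are grouped: "In the intention-to-treat, data of the participants are analyzed according to their original treatment allocation". Nothing says that all randomised participants are kept.
- Condition: if self-reported and audio "data reveal that cases are not delivered as intended, then the analyses will be performed using the per-protocol principle".
- Exclusion: a protocol deviation means "deviations from the protocol that occur in two or more sessions", and "If protocol deviations were observed, then data from this person were not included in the per-protocol analysis".

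The evidence on delivery is described under Process Evaluation. Therapists log deviations after every session, and "10 gait trainings will be randomly selected (5 implicit and 5 explicit interventions) and audio recorded". The planned dose of training is given under Training of Therapists and Treatment of Participants: "All participants will receive 9 training sessions in a 3-week intervention period". The Blinding section says that therapists know the condition they deliver and that assessors are blinded. In the Discussion (From Laboratory Setting to Clinical Practice), ITT and per-protocol analyses are announced again, this time without a condition.

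**The concern.** The primary comparison should be made in a population fixed before anyone knows how treatment went. Here two features let post-randomisation information decide it.

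First, the conditional sentence speaks of the analyses in general and does not say that per-protocol comes in addition. On a plain reading, poor fidelity would make the selected comparison the headline. Second, the attendance filter sits above both analysis sets, so even the result labelled ITT could leave out randomised participants who attended fewer than 7 sessions.

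Attendance and delivery may be related to prognosis and to arm. Excluding people on either can break the balance that randomisation provides, and two analysts following this text could report different primary results. The evidence for exclusion is also uneven. The logs cover every session but are written by unblinded therapists, while the recordings, which the plan calls objective, are very few.

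**Working it through.** **1. The plan's own figure.** Inputs from Sample Size: difference 0.16 m/s, SD 0.23 m/s, alpha 0.05 (taken as two-sided), power 0.80.

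n per group = 2 × [(1.960 + 0.842) × 0.23 / 0.16]² = 32.4, rounded up to 33. This matches the plan. The target of 40 is 33 × 1.2 = 39.6, rounded up. The sample size is not at fault, but its 20% allowance covers dropout and loss to follow-up only, not exclusion for attendance or deviations.

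**2. The rules side by side.**

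| Rule | Applies to | Depends on |
|---|---|---|
| At least 7 sessions attended | The whole statistical analysis | Post-randomisation attendance |
| ITT by allocation | Not stated to be all randomised | Allocation |
| Per-protocol if delivery was poor | The analyses | Post-randomisation fidelity data |
| Deviations in two or more sessions | Per-protocol set only | Logs and audio |

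The first row cannot hold together with ITT. The third row leaves open whether per-protocol replaces ITT or is added to it. The text also does not say whether a participant who misses exactly two sessions, and so counts as adherent with 7, has deviated in two.

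**3. What audio can contribute.** Planned sessions: 2 × 40 × 9 = 720. If a training is one session, coverage is 10/720 = 1.4%. Per arm, 5 of 360 sessions are drawn, and each participant has 9.

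- P(no recording) = C(351,5)/C(360,5) = 0.880, so P(at least one) = 0.120.
- P(exactly one) = 9 × C(351,4)/C(360,5) = 0.114.
- P(two or more) = 0.120 − 0.114, which is 0.0054 before rounding. Expected number: 80 × 0.00536 = 0.43 participants.
- P(nobody in an arm has two) = C(40,5) × 9⁵/C(360,5) = 0.793. For both arms, 0.793² = 0.629, so there is a 37% chance that at least one participant has two.
- At most two participants per arm, four in all, could have two recordings.

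If a training means a whole course, audio covers 10/80 = 12.5% of participants.

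**4. How many could be excluded.** The document gives no expected rates, so these are assumed, with sessions treated as independent.

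- Deviation rule: 1 − (1−p)⁹ − 9p(1−p)⁸. For p = 5%, 10% and 20% per session, 7%, 23% and 56% of participants leave the per-protocol set.
- Attendance filter: P(fewer than 7 of 9). For per-session attendance of 95%, 90%, 85% and 80%, 0.8%, 5.3%, 14.1% and 26.2% leave the whole analysis.

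**5. Consequence for power and error.** Power = Φ(0.16/(0.23 × √(2/m)) − 1.960).

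| Analysed per group (m) | Power |
|---|---|
| 40 | 87.5% |
| 33 | 80.7% |
| 32 | 79.5% |
| 28 | 74.0% |
| 24 | 67.4% |

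The value 32 is 40 less a true 20% loss; 28 and 24 are assumed retentions of 70% and 60%. If the more favourable of ITT and per-protocol were reported, the two-sided type I error in a simulation would be about 6.5% with 90% retained and 7.9% with 60% retained. That simulation takes exclusion as unrelated to outcome and the correlation between the two test statistics as the square root of the share retained. It does not include selection bias.

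**The case against.** The strongest reply is that the plan never says ITT will be dropped. The paragraph opens with an unconditional promise of both analyses, the Discussion repeats it, and exclusions for deviation are limited to the per-protocol set. The conditional sentence may only mean that per-protocol is run when there is something to exclude. This stands as a possible reading, so a certain switch away from ITT should not be inferred. It does not settle the matter: if per-protocol is always run, the condition has no purpose, and no primary population is named on either reading.

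A reader might also infer that the two-session rule cannot be applied because so few sessions are recorded. That goes too far. The logs are completed after every session, both sources are to be screened, and nothing requires audio alone to show two deviations. What remains is that the rule depends in practice on unblinded self-report.

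A missed session is arguably a matter of attendance, not of delivery, so the overlap at 7 of 9 sessions is an unclear point and not a proven contradiction. It might further be inferred that deviations must be commoner in one arm because any explicit instruction breaches the implicit condition. The text does not say so, and Figure 1, which lists the permitted elements, is not available here. Differential exclusion is a risk, not an established fact.

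Finally, who decides per-protocol membership, and when, is often left to a statistical analysis plan. Its absence here is not held against the article. The attendance filter and the conditional sentence are stated rules, however, and they conflict with ITT as written.

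**Conclusion.** The point holds as a failure to fix the primary population. No analysis set is primary, the role of per-protocol depends on fidelity data, and a 7-session filter on the whole analysis contradicts ITT. This should be corrected before analysis, because the text permits a selected comparison to stand as the main result.

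That a replacement of ITT will occur is not shown, and neither is an unworkable deviation rule. The audio figures (1.4% of sessions, 0.43 participants expected with two recordings) follow from the plan's numbers if a training is one session and sampling is simple random within arm. They show only that audio cannot carry the exclusion decisions. The exclusion shares, the power at reduced numbers and the type I error figures rest on assumed rates and indicate a range, not a forecast.

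**What to change.** Replace the conditional sentence and reword the paragraph so that:

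1. The primary analysis is ITT: all randomised participants, by allocation, regardless of attendance or fidelity, and always reported.
2. Per-protocol is always a secondary analysis and does not depend on what the fidelity data show.
3. The 7-session criterion is removed from the general analysis statement and placed in a single per-protocol definition, which also says whether missed sessions count as deviations.
4. Per-protocol membership is decided from the therapist logs by someone without sight of outcome data.
5. The 10 recordings are used to check the logs and describe fidelity.

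The cost is a few sentences and a short review of logs that are being kept anyway.

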## Results

The entire project was funded in September 2015. Patient enrolment began in March 2017 and is expected to continue until July 2018. Following completion of data collection, data cleaning and analyses will take place. The first study results are expected to be submitted for publication in 2019.

## Discussion

In this paper, we described the methodology of a randomized controlled single-blinded study that evaluates the potential effects of implicit motor learning compared with explicit motor learning in the gait rehabilitation of people suffering from stroke. The relevance of the study and the advantages and disadvantages of several aspects of the chosen design are discussed.

### From Laboratory Setting to Clinical Practice

Although motor learning research is growing exponentially, most published studies have been performed in laboratory settings. However, it is important to understand the application of motor learning within clinically relevant environments and the influence of interventions on the completion of everyday functional tasks [18,57]. A recent systematic review on implicit motor learning in people after stroke pointed out that studies performed within clinical settings are limited [18]. Of the 20 included studies, only 1 study involved a clinically relevant task [22]. To improve the generalizability of research findings toward clinical practice and to the broader population, various choices on different aspects in the research design had to be made. First, with regard to the task and environment, this study involves gait training that takes place at the homes of the participants. Gait is a functional daily life motor skill, and it is advised to organize practice in a context-specific environment [4,58]. Therefore, compared with the current state of evidence, this study adds insights into the effects of motor learning in a clinically relevant environment and for a clinically relevant task.

Second, in this study, the motor learning conditions are tailored to the individual participants. Most implicit motor learning studies use strict research protocols in which each participant usually receives the exact same instructions (eg, the whole experimental group receives the same right-angled triangle analogy to learn topspin forehand in table tennis), whereas the explicit learning is promoted by using the same set of verbal instructions [24]. A one-size-fits-all approach may not be ideal for the clinical population as they generally demonstrate a large variety in degree and types of impairments. The use of personalized analogies allows the physiotherapists to respond to the individual walking impairments and emphasize on the meaningful component of analogy learning. With a personalized approach (more comparable with the real-life practice), the instructions may be less standardized. Therefore, steps were undertaken to ensure the quality of the interventions. Before the study, all therapists were familiarized and trained with the implicit and explicit conditions. Measures (therapists’ logs and audio recordings of the interventions) were selected to evaluate whether the trainings were delivered as intended, and data will be analyzed as per the intention-to-treat and per-protocol (see the Data Analyses section).

### Methodological Aspects

Within this study, extra attention was given to the following 3 methodological aspects in designing the intervention: contrast, content of the interventions, and target population. First of all, it is important to address that in many rehabilitation studies, the contrast between the intervention and control group (generally usual care only) turns out to be too modest, which therefore results in neutral study results [59]. The underlying reason may be that rehabilitation interventions are often too complex to control for influences of other interventions and that the control intervention group (therapy as usual) is often poorly described. We tried to overcome these problems by including participants in the chronic phase of recovery, who do not receive additional interventions directed at the improvement of gait. Furthermore, we strive to ensure the contrast of the interventions by using a guideline, written protocol. In this protocol, the delivery of both conditions is clearly defined. It transparently describes how the 2 interventions differentiate from each other. To ensure the integrity of the intervention, the logs and audio-recorded therapy sessions will be conducted and evaluated.

Another decision we would like to address is the choice for the interventions. In clinical practice, often mixtures of implicit and explicit forms of learning are used or therapists switch between different forms of learning [15,60]. However, it remains unclear whether mixing implicit and explicit learning or switching between the forms is effective and/or necessary. The current design is necessary to evaluate the effects of implicit versus explicit learning in clinical practice, and so we believe that it is (ethically) legitimate to compare 2 distinct interventions and not use “therapy as usual” as a control intervention. The interventions in this study will be delivered in a personalized manner regarding overall components of the interventions, for example, the sort of gait impairments, amount of repetitions, and use of personalized analogies. However, the content of the interventions applied is clearly outlined in the guidelines, and therapists are required to strictly follow these.

Furthermore, within the target population, people experiencing cognitive impairments or communicative restrictions are often excluded. In this study, we strive to include a sample that reflects the broad range of impairments reported after stroke. In earlier studies, it has been shown that motor learning interventions might be effective, also for people with cognitive and/or communicative impairments [27,28].

### Implicit Motor Learning

Scientific evidence describes that implicit learning is typically characterized by robust dual-task performance, durable performance over time, and less accumulation of explicit rules [24,56]. The dual-task measure and the 1-month follow-up session were specifically chosen with respect to these implicit characteristics. First, walking while concurrently carrying out a secondary (tone counting) task [48] places high information-processing demands on the learners. In contrast to explicit learners, implicit learners showed that performance was not disrupted in dual-task conditions, which indicates that they may be able to free up attentional resources to perform the secondary task [24]. We therefore predict that the implicit condition will remain stable under secondary task burden. For this reason, implicit learning may be particularly beneficial for those who experience cognitive impairments that are commonly seen in people after stroke.

Then, a recent study by Tse et al [25] found performance improvements after a 2-day separation; however, they recommended to include a longer separation to test skill consolidation. This study will therefore evaluate performance after the 1-month follow-up period. It is hypothesized that performance improvements in the implicit group will remain robust over a longer period (1-month follow-up). To make statements about long-term effects within rehabilitation, it may be desirable for future studies to include even longer follow-up periods (>3 months). Finally, a verbal protocol will be assessed because it is hypothesized that participants within the implicit learning group will report fewer explicit rules than the control group, which would be in line with the findings of earlier studies [23,24]. Even though the starting point of the explicit intervention is to use many verbal explicit instructions and provide more details on the motor performance, the exact number of explicit rules will be tailored to the ability of the patient to process these rules. Therefore, in practice, some patients might receive higher numbers of explicit rules than others. Still, we hypothesize that the explicit group will require more explicit rules compared with the implicit group.

